#### **Possible adverse events and rescue measures**

##### **Possible adverse events**

According to the clinical experience of similar drugs at home and abroad, the clinical adverse reactions of ropivacaine analogues are very common ( $\geq 1/10$ ): Nausea, hypotension. Common clinical adverse reactions ( $\geq 1/100$ ) include: elevated body temperature, rigidity, back pain, bradycardia, tachycardia, hypertension, paresthesia, dizziness, headache, vomiting, and urinary retention. Occasionally seen clinical adverse reactions ( $\geq 1/1000$ ) include: hypothermia, fainting, anxiety, toxic symptoms of the central nervous system (convulsions, grand mal seizures, epileptic seizures, dizziness, perioral paresthesia, tongue numbness, auditory hypersensitivity, tinnitus, visual impairment, dysarticulation, muscle twitching, tremor), hypesthesia, dyspnea. Rare clinical adverse reactions ( $<1/1000$ ) include: anaphylaxis, the most serious cases are anaphylactic shock, cardiac arrest, arrhythmia.

Based on existing preclinical studies of the investigational drug, Long-acting ropivacaine injection is mainly subcutaneous, and the solvent is irritating. The main adverse reactions observed in preclinical toxicology tests included: Erythema, induration, ulceration, scab, mild acute/subacute subcutaneous inflammation, mild or mild granulation tissue formation/fibrosis.

The irritant reaction may recover after withdrawal.

**Table 7 The main adverse reactions are listed as follows:**

|                             |             |
|-----------------------------|-------------|
| Very common ( $\geq 1/10$ ) |             |
| the whole body              | naupathia   |
| circulatory system          | hypotension |

|                               |                                                                                                                                                                                                                                                                |
|-------------------------------|----------------------------------------------------------------------------------------------------------------------------------------------------------------------------------------------------------------------------------------------------------------|
| Common (1/100) or higher      |                                                                                                                                                                                                                                                                |
| the whole body                | Elevated temperature, stiffness, back pain                                                                                                                                                                                                                     |
| circulatory system            | Bradycardia, tachycardia, hypertension                                                                                                                                                                                                                         |
| central nervous system        | Paresthesia, dizziness, headache                                                                                                                                                                                                                               |
| digestive system              | emesis                                                                                                                                                                                                                                                         |
| Kidney and urinary system     | uroschesis                                                                                                                                                                                                                                                     |
| Occasional (1/1000) or higher |                                                                                                                                                                                                                                                                |
| the whole body                | hypothermia                                                                                                                                                                                                                                                    |
| circulatory system            | faint                                                                                                                                                                                                                                                          |
| central nervous system        | Anxiety, toxic symptoms of the central nervous system (convulsions, grand mal seizures, epileptic seizures, dizziness, perioral paresthesia, tongue numbness, hyperhearing, tinnitus, visual disturbances, dyskinesia, muscle twitches, tremors), hypoesthesia |
| respiratory system            | breathing difficulties                                                                                                                                                                                                                                         |
| Rare (< 1/1000)               |                                                                                                                                                                                                                                                                |
| the whole body                | Anaphylaxis, its most severe form anaphylactic shock                                                                                                                                                                                                           |
| circulatory system            | Cardiac arrest, arrhythmia                                                                                                                                                                                                                                     |

For the above adverse reactions, timely measures should be taken to ensure the safety of long-acting ropivacaine injection in the first phase I clinical study in humans, and the following risk control measures for expected adverse events should be formulated.

### **Risk management of adverse events**

The most common adverse reactions of ropivacaine injection included nausea and hypotension as well as systemic nervous system, circulatory system, respiratory system, kidney and urinary system; Occasional or rare adverse reactions: For the possible adverse reactions of ropivacaine, risk control should be focused on the following aspects in clinical studies.

- (1) First, when screening the enrolled subjects, exclude people allergic to similar drugs or belonging to allergic constitution.
- (2) Subjects should be fully informed of the possible adverse reactions caused by the treatment plan to reduce their anxiety before medication.
- (3) During and within 30 minutes after administration, clinicians with anesthesia experience should be present, and the rest of the observation period in hospital should be closely monitored by professionally trained clinical medical staff.
- (4) Ecg monitoring should be carried out when necessary.
- (5) In view of the risk of blood injection, the standard method of subcutaneous injection should be strictly followed. Before drug administration, suction should be carefully used to prevent injection into the hemostatic tube, and the injection speed should be controlled and slowly injected.
- (6) For vomiting, a common adverse reaction, subjects should eat a light diet during the test.
- (7) At the same time of injection, closely observe the patient's vital signs and continue to talk with the patient. If symptoms of poisoning appear, immediately stop the injection.
- (8) The test drug can only be opened and used once, and the remaining liquid must be discarded.
- (9) Local anesthesia will slightly affect mental status and mutual aid coordination, and temporarily impair

movement and flexibility. Therefore, subjects' free movement is restricted after administration.

(10) Measures and examinations taken to support treatment should be properly kept as original documents. Record and report in strict accordance with relevant SOP.

### **Treatment and rescue of adverse reactions**

(1) The injection must be stopped immediately in case of acute systemic toxicity.

(2) In case of central nervous system toxicity such as convulsion, emergency treatment should be carried out in accordance with professional SOP.

(3) If circulatory system toxicity reactions such as circulatory failure occur, emergency treatment should be carried out in accordance with professional SOP in time.

(4) If cardiac arrest occurs, the resuscitation time may be prolonged in order to improve the success rate of resuscitation.

(5) In case of respiratory toxicity, emergency treatment should be carried out in accordance with professional SOP.

(6) If the needle punctures the blood vessel, remove the needle immediately and press the injection site.

(7) In case of other situations, the researcher shall make corresponding emergency treatment according to the corresponding situation.

### **Serious adverse event**

#### **Definition of serious adverse events**

Serious adverse event: Refers to the adverse medical events such as death, life threatening, permanent or severe disability or loss of function, the need for hospitalization or prolonged hospitalization of the subject, and congenital abnormalities or birth defects after the subject receives the test drug.

Death: Irreversible coma or brain death, described as sudden death when the cause of death is cardiac. Death and sudden death are distinct and should not be interchanged.

Life-threatening: In the definition of "severe", the term "life-threatening" means that the patient was in danger of death at the time of the incident/reaction, it does not refer to an event/reaction that may cause death if it is assumed to be more severe in the future.

Hospitalization: Any adverse event that results in a subject's hospitalization or prolonged stay of a hospitalized subject is considered serious unless one of the following exceptions is met:

Spending time in the hospital for no more than 12 hours;

Admission to hospital is pre-planned (i.e. an operation scheduled or elective before an informed consent is signed);

Admission to a hospital, regardless of adverse events (such as being admitted for therapeutic purposes).

Disability: means a person's ability to carry out everyday life is severely impaired.

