### Termination criteria:

1.If there is any SAE associated with the investigational drug during the course of the trial, the investigator and sponsor will fully discuss the cause and determine the impact on subsequent trials before deciding whether to continue the trial.

2. According to the Evaluation Criteria for Common Adverse Events (CTCAE) (V5.0, published on November 27, 2017), if  $\geq 1/2$  of the subjects in the trial cohort have grade  $\geq$  ii adverse events or  $\geq 1/3$  of the subjects have grade  $\geq$  iii adverse events (adverse events may be determined by the investigator to be related to the test drug), the investigator and the sponsor shall discuss. Whether to terminate dose escalation;
3. If no significant adverse effects were observed in the maximum dose cohort (400mg), dose escalation was discontinued.
4. The sponsor requested a complete termination of the test;
5. The National Medical Products Administration or the ethics committee ordered the trial to be terminated for some reason.

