- (2) When the skin irritation reaction was greater than or equal to 3 minutes, observe it once every 10 minutes until the skin irritation reaction was less than or equal to 2 minutes, record the time, and continue the next dose of injection;
- (3) Skin irritation reaction  $\geq 3$  points, and no relief was observed for 2 hours, the next dose of injection was terminated, and observation or follow-up was performed until the reaction disappeared; Evaluation of local skin irritation reaction at the injection site: During the test, local skin irritation reaction at the injection site was evaluated according to the skin irritation scoring system [30], which was scored 20min, 40min, 1h, 2h,

6h, and 24h after each administration. Local skin irritation reactions were determined and recorded according to the Evaluation Criteria for Common Adverse Events (CTCAE) (V5.0, published on November 27, 2017), including pain or tenderness at the injection site, erythema or redness at the injection site, induration or swelling at the injection site, and itching at the injection site. Subjects were hospitalized for observation for at least 12 hours after single dose.

[figure not shown]

Figure 1: Schematic diagram of six zones of abdomen

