The test drug (test preparation or control preparation) shall be injected subcutaneously at a position enantiograms on the circumference; Observation of local skin irritation reaction at the injection site: The evaluation of local skin irritation reaction at the injection site was evaluated according to the skin irritation scoring system, and the scores were performed before and after administration at 20min,40min,1h,2h,6h,24h 48h 72h, as shown in the skin irritation reaction rating table.

Local skin irritation reactions, including pain or tenderness at the injection site, erythema or redness at the injection site, induration at the injection site, swelling at the injection site, itching at the injection site, etc., were determined and recorded according to the evaluation criteria for Common adverse events (CTCAE) (V5.0,

published on November 27,2017).

The onset time of analgesic maintenance time and the intensity of acupuncture pain were measured.

The linear distance between two adjacent injection sites on the same circumference was measured and recorded.

The drug administration investigator and the pain measurement investigator should not be the same person;

Subjects should be hospitalized for observation for 72 h after administration before discharge

[figure not shown]

Figure 2: Schematic diagram of four abdominal regions

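### The SAE definition has no criterion for medically important events, and the planned 72 h stay in Test 2 means a toxicity resolved on the ward need not be reported as an SAE

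*Protocol*

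**What the plan says.** The section Definition of serious adverse events covers "adverse medical events such as death, life threatening, permanent or severe disability or loss of function, the need for hospitalization or prolonged hospitalization", and adds congenital anomalies. There is no item for other medically important events. Two of the listed outcomes are then narrowed:

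- **Life-threatening** means that the subject actually faces death when the event occurs; "it does not refer to an event/reaction that may cause death if it is assumed to be more severe in the future".
- **Hospitalisation** works by cause: "Any adverse event that results in a subject's hospitalization or prolonged stay of a hospitalized subject is considered serious unless one of the following exceptions" applies. The first exception is "Spending time in the hospital for no more than 12 hours". The others are pre-planned admission and admission unrelated to an adverse event.

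For Test 2 the protocol states: "Subjects should be hospitalized for observation for 72 h after administration before discharge". For Test 1: "Subjects were hospitalized for observation for at least 12 hours after single dose".

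The section Possible adverse events names "toxic symptoms of the central nervous system (convulsions, grand mal seizures, epileptic seizures" and, among the rare reactions, anaphylaxis, cardiac arrest and arrhythmia. Treatment and rescue of adverse reactions has items for convulsion and for circulatory toxicity.

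Two actions depend on the SAE label. The section on recording and reporting SAEs requires the principal investigator to report to the sponsor within 24 hours. Termination criterion 1 begins "If there is any SAE associated with the investigational drug during the course of the trial" and then requires the investigator and sponsor to discuss the cause and decide whether to continue. Criterion 2 works on cohort fractions: at least 1/2 of subjects with related events of grade II or above, or at least 1/3 with grade III or above.

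**The concern.** This trial gives a new formulation of a local anaesthetic to healthy subjects in rising doses, and the protocol calls it the first phase I study in humans. Central nervous and cardiac toxicity are the systemic risks it describes for the drug class. A single such event is what a rapid-reporting rule is meant to catch.

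Hospitalisation is often the criterion that makes such an event serious in an outpatient setting. Here it does little work during the observation period, because all Test 2 subjects are already in the ward. If the event is also not judged an actual danger of death, and leaves no severe disability, nothing in the definition requires the label. At stake are the 24 h report and the prompt joint discussion after one event, before other subjects are dosed.

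**Working it through.** The protocol states no figure for this point. The check has two parts: follow one event through the definitions, then work out the counts that criterion 2 needs.

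**1. One event through the text.** Take a drug-related convulsion in a Test 2 subject, graded III, treated on the ward and resolved before the planned discharge.

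| Listed outcome | Met? |
|---|---|
| Death | No |
| Life-threatening | Only if the subject was actually facing death at the time |
| Permanent or severe disability or loss of function | No, since it resolved |
| Event causes hospitalisation | No, already an inpatient by plan |
| Event prolongs hospitalisation | No, resolved within the 72 h |
| Congenital anomaly | Not applicable |
| Other medically important event | No such item |

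The severity table (Table 5, for events that CTCAE does not list) does recognise this kind of event. Its grade III includes a medically serious condition that is not for the moment life-threatening. That category exists for grading only and has no counterpart in the SAE definition.

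**2. The 12 h exception.** After discharge, an admission of up to 12 h is exempt. For a subject already in the ward, the text does not say whether the 12 h means the whole stay or the added time. It is therefore unclear whether lengthening a 72 h stay by a few hours counts.

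**3. Counts needed for criterion 2.** Cohort sizes are from Table 1. The smallest qualifying count is the fraction times n, rounded up.

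- Cohorts B to E, n = 8: grade III or above, 8/3 = 2.67, so 3 subjects. Grade II or above, 8/2 = 4 subjects.
- Cohort A: 6/3 = 2 of the 6 test subjects at grade III or above, or 9/3 = 3 of 9 if controls count. At grade II or above, 6/2 = 3 of 6, or 9/2 = 4.5, so 5 of 9.

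In cohorts B to E, one event is 1/8 = 12.5% and two are 2/8 = 25%, both below 1/3. The two subjects also count towards the grade II arm, so that arm stays unmet as long as at most one other subject has a related event of grade II or above (3 of 8).

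**4. What the label changes, for illustration.** Let p be an assumed rate per subject of a related event of grade III or above that does not otherwise qualify as an SAE. The protocol gives no such rate. With n = 8 and independent subjects, P(at least 1) = 1 − (1 − p)^8, and P(at least 3) is the upper binomial tail.

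| Assumed p | P(at least 1 of 8) | P(at least 3 of 8) |
|---|---|---|
| 5% | 0.34 | 0.006 |
| 10% | 0.57 | 0.038 |
| 20% | 0.83 | 0.203 |

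If such an event counted as an SAE, the middle column would be the chance that criterion 1 calls for a discussion. Without the label, the right-hand column is the chance that the grade III arm of criterion 2 does.

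**The case against.** A reader might infer that such an event leads to no review at all, and that the dose then rises with nothing having been considered. The documents do not support that.

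- Under Table 1, safety is assessed on days 7 and 21 and the next cohort or batch depends on the results, whatever the SAE status. All adverse events are recorded, graded and assessed for causality, so the convulsion would be in front of that assessment.
- The section Drug combination requires the sponsor to be told in a timely manner of emergency drug use. The section on treatment and follow-up of adverse events also sends information to the sponsor.
- The list of outcomes is introduced by way of example, so an investigator may declare the event an SAE.
- Any event with actual danger of death, and any that prolongs the stay outside the exceptions, remains an SAE.

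It would also go too far to argue that SUSAR reporting is lost. A SUSAR must be unexpected, and these reactions are listed as known for the drug class; the investigator's manual, which would settle expectedness, is not at hand. Nor does the protocol rank convulsion among its gravest risks: it lists it as occasional.

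All of this stands and limits the point. It does not remove it. The scheduled assessments come days later, and no threshold is given for them. They act between cohorts or batches, and the Randomization section sets out batches for cohort A only. The two routes to the sponsor carry no fixed deadline. The open wording permits the label but gives the site no criterion and no duty to apply it.

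**Conclusion.** The gap is real but bounded. For a related, non-life-threatening event that resolves within the planned Test 2 stay, the protocol does not require the 24 h report or the single-event discussion under criterion 1. In cohorts B to E, 1 or 2 such events of 8 also leave criterion 2 unmet. The scheduled safety assessments and the untimed information to the sponsor remain.

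This rests on four assumptions: the events are graded III, are not judged an actual danger of death, do not prolong the stay, and are not voluntarily labelled serious. The 25% is the largest share below the threshold, not an estimate of risk. The 72 h argument concerns Test 2, which is 41 of the 44 dosed subjects (41 + 3); Test 1 plans a minimum of 12 h. In cohort A, two such events among the 6 test subjects would reach 1/3 if only test subjects are counted. The change is worth making, as a matter of reporting definition.

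**What to change.** Add one seriousness criterion to Definition of serious adverse events: any other event that is important in the investigator's medical judgement, including one that needs intervention to prevent a listed outcome, whether or not it prolongs the planned stay.

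Reconcile the hospitalisation item and its 12 h exception with the planned 72 h stay and with the risks named under Possible adverse events and Treatment and rescue of adverse reactions. In particular, state how the exception applies to a subject who is already in the ward. Carry the same wording into the SAE form guidance.

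Leave the Termination criteria as written. The change should not set a list of clinical events that automatically activates one of them, and it prescribes no treatment or stopping rule.

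The cost is a sentence or two of text and possibly a few more 24 h reports. No subjects or procedures are added.

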### **Suspicious and unexpected severe adverse reactions**

Suspected and unexpected severe adverse reactions SUSAR (Suspected Unexpected Serious Adverse Reaction) refers to a suspicious and unexpected serious adverse reaction whose nature and severity of clinical manifestations exceed information already available, such as the investigatory drug investigator's manual, the specification of the marketed drug, or the summary of product characteristics.

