### **Unexpected adverse events**

An unintended adverse event is any adverse drug event whose character or severity is inconsistent with the investigator's manual (or the control drug label). The addition of significant information about the nature or severity of known or documented adverse events is also part of the reporting of unintended adverse events. For example, events that are more special or severe than those described in the researcher's manual should be considered "unexpected".

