#### **Record and report of serious adverse events/pregnancy**

Subjects should report any serious adverse events that occur after receiving the investigational drug up to 21 days after completion of the drug.

The procedures for reporting serious adverse events are as follows:

The principal investigator had to fill out a "Serious Adverse Event Report Form" and report it to the sponsor within 24 hours of learning about SAE.

The sponsor promptly evaluates the safety information received, and reports suspicious and unexpected serious adverse reactions to all participating clinical trial researchers, clinical trial institutions and ethics committees, as well as to the drug regulatory authorities and health authorities. It is also communicated to all researchers participating in clinical trials (pharmacovigilance, data management, etc.).

Sponsors may request additional information from researchers to ensure timely and accurate completion of safety reports.

The investigator must use all necessary therapeutic measures to address SAE. Any medications required to manage SAE must be documented on the subject's case report form or in combination with the eCRF.

Each SAE should be followed up to baseline or stable or lost to follow-up, and an updated report submitted to the designated person. A simple laboratory anomaly is not reported by SAE unless the investigator considers that the anomaly meets SAE standards. Laboratory abnormalities should be recorded on the "Laboratory Data" page and periodically checked by the clinical inspector.

Pregnancy: all pregnancy after administration and its outcome (spontaneous abortion, selective termination of pregnancy, ectopic pregnancy, normal delivery or congenital malformation, etc.) should be reported to the ETHICS Committee and the sponsor in writing. Male subjects also need to report their partner's pregnancy after receiving the drug.

Pregnancy itself is not reported as an adverse event or as a serious adverse event. If the pregnancy course/outcome meets SAE criteria, the investigator should report it according to SAE reporting procedures. Pregnancy outcomes should be followed up and recorded even if subjects drop out of the study.

If pregnancy occurs within 21 days of completion of dosing, the investigator should notify the sponsor within 24 hours of the pregnancy.

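### The protocol joins nature and severity with *or* when it defines an unexpected event but with *and* when it defines a SUSAR, and the SUSAR definition does not say which reference document applies to which product

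*Protocol*

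**What the plan says.** Three parts of the protocol bear on this.

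- **Unexpected adverse events.** An unexpected event is "any adverse drug event whose character or severity is inconsistent with the investigator's manual (or the control drug label"). The example repeats the alternative form: "events that are more special or severe than those described in the researcher's manual should be considered" unexpected.
- **Suspicious and unexpected severe adverse reactions.** A SUSAR is an "unexpected serious adverse reaction whose nature and severity of clinical manifestations exceed information already available". The information meant is given by example ("such as the investigatory drug investigator's manual, the specification of the marketed drug, or the summary of product characteristics"), as an open list.
- **Record and report of serious adverse events/pregnancy.** The sponsor assesses incoming safety information promptly and "reports suspicious and unexpected serious adverse reactions to all participating clinical trial researchers, clinical trial institutions and ethics committees", and also to the drug regulatory and health authorities. No number of days is given. For any SAE, expected or not, the principal investigator must complete a form and "report it to the sponsor within 24 hours of learning about SAE".

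Two other provisions apply to SAEs whatever their expectedness. Under Ethics Committee, the investigator reports every SAE to that committee. Under Termination criteria, item 1, a drug-related SAE is discussed by investigator and sponsor before they decide whether to go on.

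**The concern.** The two definitions serve one purpose, deciding whether a reaction was foreseeable from the reference information, and they join the same two attributes differently. The SUSAR class is what sets off the sponsor's onward report. If the narrower wording is applied, a serious suspected reaction of a listed type that is worse than described, or of a new type at ordinary severity, could be held back from that report.

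This matters more here than in a study of an established product. The protocol calls this the first phase I study of the long-acting injection in humans. The preclinical Safety section says that the planned dose is above current clinical use for drug and excipients. Cohort doses run from 150 mg to 400 mg, and safety and tolerability are the first main objective. A known type of reaction in a more severe form is therefore a foreseeable signal.

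The reference source raises a second, smaller question. The SUSAR definition gives an open list that includes the label of the marketed drug and does not say for which subjects that label counts. The marketed ropivacaine hydrochloride injection is the control, a different formulation from the depot.

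**Working it through.** No figure is involved, so the check sets the two rules side by side for a serious reaction already suspected to be drug-related.

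| Compared with the reference information | Unexpected adverse events (*or*) | SUSAR definition, read literally (*and*) |
|---|---|---|
| Neither nature nor severity goes beyond it | not unexpected | not a SUSAR |
| Both go beyond it | unexpected | SUSAR |
| Only severity goes beyond it | unexpected | not a SUSAR |
| Only nature goes beyond it | unexpected | not a SUSAR |

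The rules agree in the first two rows and part in the last two. The rows are logical cases. They carry no probabilities and say nothing about how many reactions would be affected.

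**Where a case in the last two rows would go**

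1. To the sponsor within 24 hours, as for every SAE.
2. To the ethics committee from the investigator, as for every SAE.
3. To the discussion between investigator and sponsor, if judged drug-related.
4. To the drug regulatory and health authorities, the institutions and other researchers only if it is classed as a suspected unexpected serious reaction. The protocol states no other route by which an individual serious reaction reaches the authorities.

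Only step 4 depends on which rule is applied.

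**What the listed reactions show.** Under Possible adverse events, the rare reactions for ropivacaine analogues are "anaphylaxis, the most serious cases are anaphylactic shock, cardiac arrest, arrhythmia"; convulsions and seizures are listed as occasional. If the reference document lists these in the same way, a typical case is expected under both rules. The rules differ only if the reaction is more severe than described.

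**Reference source.** The section on unexpected events names the investigator's manual and, as an alternative, the control drug's label. The SUSAR definition names the manual, the marketed drug's specification or the summary of product characteristics, introduced as examples. Both accept a label. Neither pairs each source with its product outright, and in the SUSAR definition the link to the control drug is missing altogether.

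**The case against.** The strongest reply is that the SUSAR definition keeps the word *unexpected*, which the protocol defines only once, with *or*. The clause on nature and severity can then be taken as a loose gloss on that word. The English reads as a rough translation, with some table rows still partly in Chinese, so one conjunction is weak evidence that a narrower rule was intended. The reporting section uses neither the acronym nor the phrase on nature and severity, so a sponsor could go straight from it to the broader definition.

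This stands as far as it goes: a requirement for both attributes is the literal reading, not the only one. It does not remove the problem. Someone classifying a case will turn to the definition that carries the name of the class, and its specific wording is *and*. If *unexpected* already brings in the broader rule, the added clause is either redundant or narrowing, and the text does not say which.

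Three stronger conclusions might be inferred, and the documents do not support them.

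- *Serious reactions would escape expedited reporting.* All SAEs still reach the sponsor and the ethics committee, and the protocol sets no expedited deadline for SUSARs that could be missed.
- *Admitting the marketed label contradicts the section on unexpected events.* That section accepts the control drug's label itself. Manual for the test drug and label for the control is a natural reading of the list. The fault is that sources are not assigned to products.
- *Any convulsion or cardiac arrest after the depot would be lost because it is listed.* Whether it is expected depends on the investigator's manual, which is not at hand, and a typical listed case may be expected under either rule.

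**Conclusion.** The inconsistency is real, and it sits in an operative safety-reporting rule. On the literal reading, a serious suspected reaction that exceeds known information in severity alone, or in nature alone, is unexpected by one definition and not a SUSAR by the other. It could then be left out of the sponsor's onward report to authorities, institutions and other researchers. In addition, the marketed drug's label could be used to judge expectedness for the depot, because the SUSAR definition does not confine it to control subjects.

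The size is limited. The conclusion assumes that the SUSAR wording is applied as written. The other safeguards remain, no count of affected cases can be derived, and no endpoint, sample size, analysis or escalation rule changes. It is a wording conflict worth settling before a case arises.

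**What to change.** In the section on suspicious and unexpected severe adverse reactions, replace *nature and severity* with *nature or severity*, to match the section on unexpected adverse events. In the same place, state that expectedness is judged against the investigator's manual for the test product and against the marketed drug's label for control subjects. The reporting section can stay as it is.

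The cost is a short wording amendment with its usual approvals, and possibly a few more onward reports. Data collection and analysis are untouched.
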